### Training, coaching, and mentorship for HCWs implementing QI in clinics randomized to the intervention arm

The QI approach promotes front-line staff engagement in the identification of problems affecting performance and catalyzing rapid cycle testing of possible solutions in each of the eight identified TB-HIV integration indicators (Table 1). The QI team at each of the intervention clinics will include the PHC supervisor from the District Health Management team, the QI clinic champion, the clinic’s operation manager, selected clinic staff members, and a QI coach/mentor represented by a member of the study team. The QI champion, usually a clinic’s most senior nursing staff, will be trained to lead and support QI teams in their facilities using QI methods including the PDSA model, systems thinking, and the use of data for improvement.

The QI mentor and champion will be capacitated by the research team to provide peer-leadership and mentorship for implementation of QI methodology. In addition, they will also be capacitated to monitor the weekly performance of their clinics in achieving key successes on the indicators being targeted for improvement. The QI teams will be established through training of selected health workers to become fully fledged QI leaders and implementers within their facilities. Only HCWs experienced in both TB-HIV management and implementation of national TB and HIV guidelines would be eligible for QI training.

### Implementation of the intervention

Three collaborative learning sessions and additional QI support (mentoring and coaching) visits at specific time points during the study period (Fig. 1) will be pre-arranged. Collaborative learning session one will coach teams in the use of a range of QI methods and tools (process mapping, fishbone system analysis, PDSA cycles, use of line graphs, and other data for improvement). Areas requiring improvement will be identified and prioritized, and aim statements encompassing specific aims and targets will be developed. Brainstorming by the QI team and process mapping will be done to define a strategy to effect positive change (“a change idea”). The PDSA cycles tracking a set of predefined indicators will be reviewed bi-weekly by the QI team to test if the recently adopted change idea resulted in performance improvement, throughout the study period. This will enable the generation of new ideas for improvement, iterative testing of these ideas, and monitoring of progress attained through use of run charts and graphs. Learning session two, scheduled 6 months later will review learnings for all successful change ideas and challenges against overall clinic performance, with the goal of scaling back on frequency of QI support meetings for clinics that are undertaking reliable improvement work. Learning session three, scheduled at month 12, will be focused on review and scalability of the final successful change package. It is anticipated that after learning session three, the clinic’s QI teams would sustain successful change ideas. Lessons learned will also be shared and documented across the intervention teams. At the successful conclusion of the projects, the intention is to scale up a reliable “change package” of successful, tested changes across all clinics in the two districts, if not across the entire district.

### Standard of care in the control clinics: description of TB, HIV, and integration services

Since the 2009 endorsement of integrated TB-HIV services by the South African National AIDS Council (SANAC) [48], and adoption of TB-HIV service integration into policy and practice by the National Department of Health (NDoH) [29], South African guidelines recommend integration of TB and HIV services by a single service provider [8, 49].

### Data collection

Data on TB-HIV integration indicators will be obtained from patient files and existing standard customized electronic data management systems supported by SA DoH [4, 41]. Routine clinical information is recorded in paper-based registers and patient clinic folders housed in clinics and subsequently captured onto the relevant TB or HIV electronic system supported by SA DoH. Baseline patient level data will be collected retrospectively for the 12 months prior to study start and will continue prospectively throughout the study period (Tables 2 and 3). In addition, HCW interviews will be conducted, using case report forms, at specific time points during study period from consenting health workers in both the intervention and control clinics. Table 2 summarizes the data to be collected, data source, and outcome measures while Table 3 presents the study’s schedule of activities.

**Table 2 Tab2:** Data collection tools, sources, and outcome measures

Data to be collected	Data source	Outcomes measure
TB-HIV integration indicators		Clinical outcomes
	TIER.Net, community care givers, autopsy reports	- Mortality rates—number of deaths among TB and HIV patients accessing care in study clinics from date clinic enrolled to 18 months post enrolment.
	TIER.Net	- Proportion of patients retained in care—proportion of HIV-infected patients enrolled in care at clinics and alive 12 months.
	TIER.Net	- Viral load testing coverage—proportion of patients on ART with viral loads test done among those eligible for viral load test at requested time points.
	TIER.Net	- Viral load suppression—proportion of patients with undetectable viral load tests among those receiving 12 monthly viral load test.
	TIER.Net and clinic TB registers	- TB treatment outcomes at end of study period— - Cure rates: proportion of new smear-positive patients that are smear-negative in the last month of treatment and on at least one other occasion at least 30 days prior. - Loss to follow-up rates: proportion of new smear-positive patients that interrupted TB treatment for 2 consecutive months or more. - Treatment failure rates: Proportion of new smear-positive patients that are smear-positive at the end of TB treatment period. - Death rate: proportion of new smear-positive patients that died during TB treatment. - Transfer-out rate: proportion of new smear-positive pulmonary TB patients registered that were transferred to another district and for whom the TB treatment outcome is unknown.
		*Process outcome* - HCT Coverage—proportion of patients with unknown HIV status tested for HIV
	TIER.Net, DHIS and clinic-based registers	
	TIER.Net, DHIS and clinic-based registers	- Co-infection—proportion of TB patients co-infected with HIV
	TIER.Net, DHIS and clinic-based registers	- Time to ART initiation (in days)—time in days between diagnosis of HIV infection diagnosis and ART initiation.
	TIER.Net, DHIS and clinic-based registers	- TB screening coverage among HIV-infected patients— a) Proportion of HIV-infected patients receiving TB screening and b) Frequency of TB screening during follow-up
	TIER.Net, DHIS and clinic-based registers	- IPT initiation— a) Proportion of HIV-infected TB negative patients initiated on IPT and b) Proportion of patients completing IPT course.
	TIER.Net, DHIS and clinic-based registers	- CPT uptake among co-infected patients—proportion of eligible HIV-positive patients initiated on CPT
TB-HIV service integration in the facility macro-environment	Survey instrument developed by Uyei et al. 2014 [7]	Measured TB-HIV integration in terms of: ➢ Organization—such as co-location of services, combined patient records, information management, and joint training ➢ Structure—existent practice of joint service delivery, ➢ Process—behavior and practice of delivering services ➢ Culture—work place culture and personal identification with integrated service delivery
Clinic profile tool aimed at assessing clinics’ infrastructure, capacity, and systems in place to implement TB-HIV integration services	A CAPRISA designed tool	- Resources inventory and needs for implementation of TB-HIV integration services, e.g., available guidelines, protocols, policies, trained staff. - Existing quality improvement interventions, processes and measurements - District level leadership and support
Clinic culture, leadership, resources, etc.	The COACH tool designed by Bergstrom et al. 2015 [56]	- Clinic leadership and support - Staff knowledge and skills - Perceptions of work culture at PHC
Staff Work-related Quality of Life	WHO Work-related Quality of Life Scale	Work-related quality of life for staff at PHC

**Table 3 Tab3:** Study schedule of activities

Study activity	Study time points			
	Baseline (0–1 month)	6–7th month	12–13th month	Monthly (1st–18th month)
Retrospective collection of 12 months data on TB-HIV indicators from TIER.Net*, DHIS** and clinic-based registers	X			
***QI Learning Collaborative (Intervention Clinics Only)	X	X	X	
Monthly downloads of data on TB-HIV indicators from TIER.Net*, DHIS** and clinic-based registers				X
Clinic Profile Survey	X	X	X	
TB/HIV Service Integration Survey	X	X	X	
Work-related Quality of Life Survey	X	X	X	
Context Assessment Survey	X	X	X	
Quality Improvement Survey (Intervention Clinics Only)	X	X	X	

*TIER.Net—Three Inter-Linked Electronic Register for Tuberculosis

**DHIS—District Health Information System

***QI Learning Collaborative—use of PDSA cycles, run charts, process mapping

### Study outcome measures

The primary outcome of this study will be all-cause mortality rate among patients newly diagnosed with TB and/or HIV. Secondary outcomes will include time to ART initiation, retention in care, IPT and CPT uptake as per the current SA DoH guidelines, TB cure rates, viral load testing rates, and viral load suppression rates.

### Sample size estimation

We anticipate that about 6000 HIV-positive patients will be diagnosed with active TB in the study population during a 12-month period. This is based on the assumption that between 100 and 200 new TB-HIV co-infected patients are seen in each of the 40 clinics per year. This translates to an average of 350 patients per cluster (assume unequal cluster sizes). Assuming a case fatality rate of 15% in the control arm, coefficient of variation between 0.25 and 0.35, and a type I error rate of 5%, we will have 80% power to detect a 30% reduction in mortality. The chances of detecting other levels of effectiveness are shown in Table 4.

**Table 4 Tab4:** Power to detect different levels of effectiveness (keeping number of events constant)

Reduction in mortality (%)	Power to detect an effect (%)
10	13
20	42
30	80
40	98

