### Study setting and design

This is an open-label cluster randomized controlled trial where the cluster is defined as the group of clinic(s) under the same PHC clinic supervisor, where each of the 16 PHC clinic supervisors may oversee between 3 and 5 PHC clinics. Cluster randomization was chosen for practical reasons because the study will be carried out in pragmatic settings involving 40 PHC clinics within the King Cetshwayo district (formerly called uThungulu) [34] and Ugu districts in KwaZulu-Natal, South Africa. A total of 11.1 million people (19.9% of the South African population) live in KwaZulu-Natal [35]. The province has the highest TB-HIV disease burden in South Africa with an estimated TB-HIV co-infection rate of 70% [12, 36]. The two districts were selected because they are rural with high burden of TB, HIV, and TB-HIV co-infection, despite TB and HIV treatment services in accordance with current guidelines being available [13, 14, 37]. In 2016, 82.3% of TB-HIV co-infected patients were initiated on ART in KwaZulu-Natal, slightly lower than the national ART initiation rate of 84.5% [38]. King Cetshwayo district, located on the northern coast of KwaZulu-Natal, has a population of 937,793, with approximately 80% living in rural settings [39]. Similarly, Ugu district, situated in southern KwaZulu-Natal has 86% of its population of 750,214 living in rural areas [38, 40]. The in-hospital case fatality rate due to TB-HIV co-infection in both King Cetshwayo district (38.4%) and Ugu district (38.8%) remains high despite ART availability [27]. In 2015, over a quarter of all deaths in KwaZulu-Natal, irrespective of age or gender, were caused by TB (15.5%) or HIV (12.2%). PHC clinics offer community level frontline services and chronic care for all health ailments, including TB and HIV. Patient level data for these diseases are routinely captured electronically [41].

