### Randomization and study groups

Randomization will occur at the level of the PHC supervisor. This is being done to avoid contamination of intervention effects into control clinics since each supervisor routinely supports multiple clinics. Each PHC clinic supervisor will be randomly assigned in a 1:1 ratio to the intervention or control arm. The study investigators would provide a list of facilities and supervisors to be randomized using a computer-generated randomization list generated by study statistician. In South Africa, a PHC clinic supervisor fulfills a management role at PHC clinics [42], and are mandated to ensure smooth clinic operations through oversight of clinic performance against set targets including patient clinical outcomes and programme performance targets, and oversees the implementation of clinical guidelines. Each PHC clinic supervisor may oversee between three and five PHC clinics within one district. Therefore, through randomization of 14–16 PHC clinic supervisors working in both the Ugu district and King Cetshwayo district, 40 clinics (20 in each arm) will be enrolled into this study as each supervisor oversees on average three to five medium-sized clinics. Not all clinics under the purview of the PHC clinic supervisors randomized will be enrolled into the study. Clinics will be excluded if ART services are not offered on site, services are run by a single nurse, and if they are mobile clinics or clinics located within hospitals. All eligible clinics enrolled in the control arm of this trial will receive the prevailing standard-of-care for TB-HIV integration (Fig. 2) in accordance with the DoH guidelines. While the study team will not interfere with any additional benefit that control clinics may receive (for example, support from other NGOs), changes to the background standard of care will be recorded systematically and accounted for in the final analysis.

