### Statistical analysis

The primary outcome of mortality and secondary outcomes will be analyzed using cluster-summary methods. The primary outcome will be analyzed among TB-HIV co-infected patients only while the secondary outcomes will be analyzed among TB-HIV co-infected, HIV-only, and TB-only patients. Mortality rate per arm will be calculated as geometric mean of cluster-level summaries and will be compared using unpaired *t* test. The same technique will be applied to secondary outcomes. The *t* test applied in cluster-level summaries is one of the robust methods of analyzing unmatched trials especially when there are small number of clusters per arm [50]. Since we have 16 clusters and 40 sub-clusters, multi-level regression will be used as secondary analyses. Proportional hazard regression with random effects (frailty models) will be used for analyses of time-to-event outcomes. Generalized estimating equations and mixed effects linear models will be used for binary and quantitative outcomes, respectively. These models will take the clustering by PHC supervisor and clinic into account through the random effects. They will also allow us to adjust for baseline variables, especially those with imbalance between arms, as this is likely when clusters are fewer. The HCW interviews will be summarized using descriptive statistics such as means and frequencies. Adjusted baseline descriptive statistics will be calculated as the means of the cluster-level summaries and characteristics of the two arms will be compared using *t* test or rank sum tests. Individual-level summaries at baseline will be compared using *t* test or rank sum tests and Fisher’s exact test. Data will be analyzed with SAS version 9.4 (or higher) (SAS Institute INC., Cary N.C, USA).

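### With 8 supervisor clusters per arm and the planned t test, the stated 80% power for a 30% mortality reduction, and Table 4, do not hold across the stated CV range

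*Protocol article*

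**What the plan says.** Study setting and design fixes the unit: "the cluster is defined as the group of clinic(s) under the same PHC clinic supervisor". Randomization and study groups allocates supervisors 1:1 and gives their number as a range: "through randomization of 14–16 PHC clinic supervisors working in both the Ugu district and King Cetshwayo district". Statistical analysis uses the upper figure ("Since we have 16 clusters and 40 sub-clusters, multi-level regression will be used as secondary analyses") and makes the primary comparison an unpaired t test on cluster-level summaries, with geometric means per arm.

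Sample size estimation gives the inputs:
- about 6000 co-infected patients in 12 months, from 40 clinics with 100 to 200 each;
- a mean cluster size of 350, sizes taken as unequal;
- control-arm mortality of 15%;
- for the variation between units, "coefficient of variation between 0.25 and 0.35", which is not defined further;
- for the significance level, 5%, with no sidedness given.

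The result is a single figure: "we will have 80% power to detect a 30% reduction in mortality". Table 4 gives power of 13, 42, 80 and 98% for reductions of 10, 20, 30 and 40%, with the number of events held constant.

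**The concern.** One power figure is attached to a CV range over which power should move by about 20 percentage points. With few clusters, between-cluster variation dominates the variance, so the number of supervisors and the CV decide the power, and patient numbers add little. Eight clusters per arm looked too few for 80% at CVs of this size.

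This is the power of the primary mortality comparison. If it is overstated, a non-significant result may be read as coming from a trial with 80% power against a 30% reduction, when the chance of detecting that reduction was materially lower.

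**Working it through.** **Inputs.** p0 = 0.15; p1 = 0.15 × 0.70 = 0.105; m = 350 per cluster; k = 0.25, 0.30, 0.35; c = 8 per arm (16 supervisors) or 7 (14 supervisors). All are from the protocol. Two-sided 5% is an assumption.

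**1. Table 4 itself.** Under a normal approximation each row implies SE(log RR) = −ln(1−r)/(1.96 + z_power):
- 10%: 0.1054/(1.960 − 1.126) = 0.126
- 20%: 0.2231/(1.960 − 0.202) = 0.127
- 30%: 0.3567/(1.960 + 0.842) = 0.127
- 40%: 0.5108/(1.960 + 2.054) = 0.127

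So Table 4 behaves like a normal approximation with one constant SE of about 0.127. Several routes lead there:

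| Route | 10% | 20% | 30% | 40% |
|---|---|---|---|---|
| Table 4 | 13 | 42 | 80 | 98 |
| 8 supervisors per arm, observed CV 0.254: SE = 0.254 × √(2/8) = 0.127 | 12.9 | 42.0 | 80.2 | 98.0 |
| 20 clinics per arm, 150 patients each, CV 0.32, c−1 formula (step 2) | 13.5 | 43.3 | 79.9 | 97.3 |
| 247 effective events: SE = √(4/247) = 0.127 | 12.9 | 41.8 | 80.0 | 98.0 |

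The third route would mean a design effect of about 765/247 = 3.1, where 765 = 3000 × 0.15 + 3000 × 0.105.

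**2. Planned test, between-cluster CV.** On the log scale, to match the geometric means:

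V = (1−p0)/(m·p0) + (1−p1)/(m·p1) + 2k² = 0.0162 + 0.0244 + 2k²

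SE = √(V/c); δ = 0.3567/SE; power from the noncentral t with 2(c−1) = 14 df and critical value 2.145.

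| k | V | SE | δ | Power |
|---|---|---|---|---|
| 0.25 | 0.1655 | 0.1439 | 2.48 | 63.6% |
| 0.30 | 0.2205 | 0.1660 | 2.15 | 51.6% |
| 0.35 | 0.2855 | 0.1889 | 1.89 | 42.0% |

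Cross-check with the usual cluster formula on proportions, power = Φ(0.045/√(v/(c−1)) − 1.96), where v = p0(1−p0)/m + p1(1−p1)/m + k²(p0² + p1²). For k = 0.25, v = 0.002728 and power is 62.5%; for 0.30, v = 0.003650 and 50.4%; for 0.35, v = 0.004740 and 40.9%. Without the c−1 correction the figures are 68, 56 and 46%.

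**3. Fourteen supervisors** (c = 7, 12 df). At m = 350: 56.8, 45.6 and 36.9%. If the 6000 patients are shared among 14 clusters (429 each): 58.8, 46.8 and 37.7%.

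**4. Observed-CV reading.** If the CV already includes sampling variation, V = 2k² and, for c = 8, SE = k/2:

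| k | SE | δ | t test, 14 df | Normal approximation |
|---|---|---|---|---|
| 0.25 | 0.125 | 2.85 | 75.6% | 81.4% |
| 0.30 | 0.150 | 2.38 | 60.0% | 66.2% |
| 0.35 | 0.175 | 2.04 | 47.5% | 53.1% |

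These are also the limits of step 2 as m grows without bound, so larger clusters cannot restore 80% with the planned test.

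**5. Solving back, 8 per arm, t test.** For 80% power at a 30% reduction, the between-cluster CV would have to be about 0.19. The reduction detectable with 80% power is 35.4, 39.7 and 43.8% at k = 0.25, 0.30 and 0.35 (between-cluster CV), or 31.4, 36.4 and 41.0% (observed CV).

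**6. Patients per cluster.** 6000/16 = 375, not 350. Using 375 at k = 0.25 moves power from 63.6% to 64.3%.

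**The case against.** The protocol does not define its CV. Read as the CV of observed cluster rates, with 8 supervisors per arm and a normal approximation, a CV of 0.254 gives all four Table 4 values after rounding. The stated figures may therefore come from the correct units at a CV inside the stated range. This stands, and it rules out two stronger claims that a reader might make:

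- *That the calculation counted 40 clinics as independent units.* The clinic-level figures come close, but only with a CV chosen to give 80%, and the supervisor-level route fits slightly better. The document does not say which was used.
- *That 80% requires a CV of 0.19 on any reading.* That value belongs to the between-cluster definition with the t test.

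The objection does not rescue the statement. A normal approximation is not the planned test: with 14 df the same reading gives 75.6% at CV 0.25. At 0.35 it gives 47.5%, or 53.1% even with the normal approximation.

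Sidedness is also unstated. One-sided 5% with the observed CV and the t test (critical value 1.761) would give about 86% at CV 0.25, but about 62% at 0.35. One-sided testing is not declared, and it fits Table 4 poorly: the one-sided, uncorrected between-cluster calculation at CV 0.25 gives 18.4% and 46.5% in the first two rows, against 13 and 42.

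The 350 may be a deliberate allowance for unequal cluster sizes, so the gap from 375 is not shown to be an error.

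Finally, a fuller calculation may sit in a document not shown. The point is not an omission, however: the printed inputs and the printed result do not agree across the printed range.

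**Conclusion.** The point holds. With 8 supervisor clusters per arm and the planned t test at two-sided 5%, power for a 30% reduction is about 64, 52 and 42% at between-cluster CVs of 0.25, 0.30 and 0.35. With 14 supervisors it is about 57, 46 and 37%. On the observed-CV reading it runs from about 76% to 48%. Within the stated range, a two-sided 80% appears only with a normal approximation at a CV of about 0.25. Unequal cluster sizes, which the protocol itself assumes, would generally lower power further.

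The range of about 42-64% should not be quoted as the trial's true power: it depends on two-sided testing and on the between-cluster meaning of the CV, neither of which the protocol states. What does not depend on the CV definition is that, at two-sided 5%, the planned test stays below 80% throughout the stated range and loses more than 20 points across it. The source of Table 4 remains undetermined.

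**What to change.** In Sample size estimation:

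1. State whether the 5% is two-sided, and whether the CV is the between-cluster CV of true rates or the CV of observed cluster rates.
2. Restate the power sentence and Table 4 for 8 and 7 supervisor clusters per arm, using the planned t test (14 and 12 df) and showing both ends of the CV range. For two-sided 5%, 350 per cluster and the between-cluster CV, counting both rejection tails, the values (%) are about:

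| Reduction | 8 per arm, CV 0.25 / 0.35 | 7 per arm, CV 0.25 / 0.35 |
|---|---|---|
| 10% | 11 / 8 | 10 / 8 |
| 20% | 31 / 20 | 27 / 18 |
| 30% | 64 / 42 | 57 / 37 |
| 40% | 90 / 70 | 85 / 63 |

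3. State that, with 8 per arm, 80% power applies to a reduction of about 35-44%, or about 31-41% if the CV is the observed one.
4. Explain 350 per cluster or reconcile it with 6000/16 = 375. This is minor and moves power by less than one point.

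The change is wording and one table. Enrolment, conduct and analysis are unaffected; the only cost is a less favourable stated power.
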